### 6.2.1 Method of assignment to treatment/intervention (randomization, stratification)

After written informed consent given participants will be randomized with a 1:1 ratio in either treatment group. Randomization is done by designated study staff drawing a sealed envelope containing a randomization card or electronically. Patients are informed about the assignment by the investigators.

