### 8.3 Compliance with study intervention

We assess the auto-declared compliance of the patients in the intervention (decolonization) arm via questionnaires and by recuperating the empty packages of the decolonization sets.

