### 9. STUDY ASSESSMENTS

#### 9.1 Assessment of primary outcome

Judged by local wound healing (healed vs delayed wound healing according to Reference). The wound healing will be assessed visually by orthopaedic surgeons. Wound nurses and the study investigators may help in the assessment of wound problems, but in case of doubtful cases, the opinion of the treating physician will dominate the decision upon the presence or absence of wound problems and/or infection.

Persistent postsurgical pain, serum laboratory markers, or the patient's subjective wound feelings will not serve as objective criteria for wound healing (or in the contrary, wound discharge and dehiscence). A wound problem solely due to stitches and localized suture problems will not count as a wound problem. A keloid or altered pigment features will not be counted as a problem in this trial. Remission is defined as the absence of any problems and as the absence of any clinical signs of infection.

The primary outcome will be assessed on both, the Intention-to-treat and the per-protocol populations.

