### **11.2 Determination of Sample Size**

In our hospital, postoperative wound problems occur in at least 5% percent of all interventions. Incidence for both, revision surgery and/or SSI, in our selected patient population is set for 10% according to our clinical experience among the selected patient population that composes our study population.

We perform a superiority RCT with a power of 80% in favor of the decolonization. With 95% event-free surgeries in the decolonization arm versus 90% in the standard arm, we formally need 2 x 474 orthopedic surgery episodes, which we sum up to 2 x 500 surgeries (n = 1'000). A patient can be included several times as long as he/she gets not infected and has not witnessed postoperative wound problems.

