### 11.3 Planned Analyses

All analyses will be performed for the entire study population. In a second step, all analyses will be separately performed according to subgroups of patients, based on the type of orthopaedic surgical procedure (e.g. arthroplasties, implant-related surgeries, etc.). We will use descriptive statistics and will perform group comparisons (using the Pearson- $\chi^2$ -test, the Fischer-exact-test, or the Wilcoxon-ranksum-test), as appropriate. We will also perform composite (SSI and wound problems) and separate (SSI or wound problems) multivariate analysis using a Cox regression model targeting the co-primary outcome variables. For the primary outcome parameter, univariable and multivariable results will be computed using a Cox regression analysis. Variables with a  $p$  value  $\leq 0.2$  in univariate analysis will be included in a stepwise forward selection process for multivariate analysis. Key variables will be checked for co-linearity and interaction. The number of variables in the final model is limited to the ratio of 1 variable to 5 to 8 outcome events. The significance level is  $p \leq 0.05$  (two-tailed).

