#### 11.3.2 Final analyses

The intent-to-treat (ITT) population will consist of all randomized patients. Patients will be analysed according to treatment group assignment. Patient disposition and baseline characteristics will be based on the ITT population.

The per-protocol (PP) population will consist of all randomized patients who complete the study (or who are otherwise defined as a treatment failure) according to the clinical investigation plan and who have not deviated significantly from the protocol. All efficacy analyses will be repeated using the PP population. Any analysis involving microbiological assessments will exclude patients without an assigned baseline pathogen.

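### No analysis set is named to carry the superiority claim, adherence exclusions can fall only on the decolonization arm, and section 11.4 lets the same exclusions into the ITT set

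*Protocol*

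**What the plan says.** The protocol describes a superiority trial of decolonization against no decolonization. Section 9.1 places the primary outcome on two populations: "The primary outcome will be assessed on both, the Intention-to-treat and the per-protocol populations". The synopsis also lists both, unranked.

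Section 11.3.2 defines ITT as everyone randomised, analysed as assigned. PP consists of completers (or treatment failures) "who have not deviated significantly from the protocol. All efficacy analyses will be repeated using the PP population". No threshold for a significant deviation is given.

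On adherence, section 8.3 says: "We assess the auto-declared compliance of the patients in the intervention (decolonization) arm via questionnaires", supplemented by the return of used packages. Under section 8.1.2 the control arm receives neither decolonization nor the questionnaire.

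Section 11.4 adds two rules. Patients with missing outcome or decolonization data become drop-outs, and patients with major deviations are removed from the ITT set as well as the PP set.

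**The concern.** In a superiority trial the analysis set matters most when ITT and PP disagree, and the protocol does not say what follows then.

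The PP set is also not neutral between the arms. A control patient has no decolonization schedule to miss and no compliance record. Exclusion for non-adherence, which happens after randomisation, can therefore remove patients only from the decolonization arm. If those who do not complete the regimen are also more prone to wound problems, the remaining decolonized patients are a lower-risk group than the controls, and a difference appears without any effect of the set.

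Naming ITT would normally settle this. Here it does not, because section 11.4 can take the same patients out of ITT. What is at stake is whether the primary comparison keeps the protection of randomisation.

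**Working it through.** **1. The protocol's own figure.** Inputs from section 11.2: "We perform a superiority RCT with a power of 80% in favor of the decolonization" and "With 95% event-free surgeries in the decolonization arm versus 90% in the standard arm, we formally need 2 x 474 orthopedic surgery episodes". The two-sided 0.05 level is in section 11.3.

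Uncorrected size per arm: n = [1.960·√(2·0.075·0.925) + 0.842·√(0.10·0.90 + 0.05·0.95)]² / 0.05² = (0.730 + 0.312)² / 0.0025 ≈ 434.4, i.e. 435.

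With continuity correction: (434.4/4)·[1 + √(1 + 4/(434.4·0.05))]² ≈ 473.6, i.e. 474. The stated figure is reproduced. At the planned 500 per arm, power is 85%, or 82% with the correction.

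**2. What one-sided adherence exclusion does when there is no effect.** From the protocol: 10% risk, 500 per arm, two-sided 0.05. Assumed, because the protocol gives no figures: non-adherent share f in the decolonization arm, and relative risk r of non-adherent against adherent patients.

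Keeping the whole arm at 10%, the adherent patients' risk is 0.10 / (1 − f + f·r). For f = 20%, r = 2 this is 0.10/1.2 = 8.3%, so PP compares 8.3% with 10%. The spurious difference is 1.7 points, a third of the planned 5.

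Check of that case by normal approximation, with 400 against 500 episodes:
- pooled risk (33.3 + 50)/900 = 0.0926;
- null standard error √(0.0926·0.9074·(1/400 + 1/500)) = 0.01944;
- standard error under the shifted risks √(0.0833·0.9167/400 + 0.09/500) = 0.01926;
- chance of a significant false benefit Φ[(0.01667 − 1.96·0.01944)/0.01926] = Φ(−1.11) ≈ 13.3%.

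Simulation (200,000 trials per case, uncorrected chi-square, non-adherers removed from the decolonization arm only) gives the chance that PP falsely favours decolonization, nominal 2.5%:

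| Non-adherent share | r = 0.67 | r = 1 | r = 1.5 | r = 2 |
|---|---|---|---|---|
| 10% | 1.6% | 2.5% | 4.3% | 6.8% |
| 20% | 1.0% | 2.5% | 6.5% | 13.3% |
| 30% | 0.7% | 2.4% | 9.1% | 20.7% |

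ITT of all randomised stays at about 2.5% in every cell. The simulation treats episodes as independent and uses the chi-square test, not the Cox model.

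**3. Whether ITT is protected.** Section 11.3.2 puts every randomised patient in ITT; section 11.4 removes major deviators from it. Both cannot hold. Section 11.4 also makes missing decolonization data a reason for drop-out, and such data are collected in one arm only. If non-adherence is judged a major deviation, ITT loses the same patients as PP and the table applies to it too. If it never is, and no decolonization data are missing, ITT keeps its 2.5% as far as adherence is concerned. The text does not say which.

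**The case against.** **ITT already leads.** Section 11.3.2 defines ITT first, bases disposition and baseline on it, and describes the PP efficacy analyses as a repeat. That is a fair hint, but it is not a designation, and section 9.1 and the synopsis give none.

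**The choice belongs in the analysis plan.** Reporting both sets is ordinary practice, and the deciding set and deviation criteria are often fixed later. If that were all, the point would be minor. The conflict between 11.3.2 and 11.4 over who is in ITT, however, is stated in the protocol itself.

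**Stronger readings that a reader might infer:**
- *PP favours decolonization whatever the set does.* Not supported. It requires non-adherers to be at higher risk. With a demanding regimen and a frail population that is plausible, but the protocol does not say it. At equal risk there is no bias; at lower risk it reverses.
- *Success on either set is enough.* No such rule is stated, and assessing both could equally mean that both must agree. Under an either-set rule with r = 1, two-sided error would be 6.0%, 6.6% and 7.0% for 10%, 20% and 30% non-adherence, but that rule would be the reader's own.
- *PP sets adherent decolonized patients against all controls.* Too strong. Controls can leave PP for incomplete follow-up or other deviations. Only the adherence part is one-sided, and the simulation isolates that part.
- *PP should be replaced by a complier effect.* This is a preference. It relies on self-declared adherence and on allocation acting only through use of the set, which is open to doubt in an unblinded trial.

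**Conclusion.** The concern holds in conditional form. The protocol does not name the set that supports superiority, adherence exclusions from PP are one-sided by design, and section 11.4 contradicts section 11.3.2 in a way that can carry the same selection into ITT.

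With no true effect, the false-benefit rate in a set thinned in this way is about 4–9% at a relative risk of 1.5 and 7–21% at 2, against 2.5%. It is about 2.5% at equal risk and 0.7–1.6% at 0.67. These figures rest on an assumed non-adherence of 10–30% and on the assumed relative risks. They show what the wording permits and do not predict this trial's result. The contradiction over ITT membership rests on no assumption.

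**What to change.** - **Sections 9.1 and 11.3.2:** state that superiority is concluded only from the ITT analysis of all randomised episodes, analysed as assigned.
- **Section 11.4:** delete the removal of major deviations from the ITT set, and delete drop-out for missing decolonization data. Without this change, naming ITT as primary does not solve the problem. Missing outcome data can arise in either arm and are a separate matter.
- **PP:** label it supportive and unable to establish superiority on its own, with the deviations that lead to exclusion defined in advance.
- **Optional:** a complier average causal effect as a sensitivity analysis, using the questionnaire and returned-package data already planned, with its assumptions stated. It is not required.

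The cost is wording in three sections, with no added patients, visits or data. The sample size calculation is unaffected.

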#### 9.1.2 Assessment of other outcomes of interest

Secondary objectives are adverse events, unplanned revision surgery for non-infection problems in same time period, and the subjective opinion on the decolonization (only for patients being decolonized). We will note them during the study visits and per questionnaires (for the patients participating in the decolonization).

#### 9.1.3 Assessment of safety outcomes

##### 9.1.3.1 Adverse events

See chapter 10

##### 9.1.3.2 Laboratory parameters

n/a. No study specific laboratory parameters will be assessed

##### 9.1.3.3 Vital signs

n/a. No study specific vital sign measurements will be performed. These vital signs are however col-

lected and noted several times per day according to the clinical protocols of the operated patients for various reasons. We will not add additional criteria in terms of the vital signs only for the sake of our trial.

#### **9.1.4 Assessments in participants who prematurely stop the study**

Participants who prematurely stop the investigation are defined as patients who withdraw consent or who, in the opinion of the investigator, are no longer eligible to participate in the study. Where possible, such patients will complete an early-termination visit to undergo all assessments applicable to the corresponding (or next) scheduled study visit. For these patients, we will record eventual adverse events, physical examination, laboratory parameters, vital signs during a follow-up period determined by clinical control, which is usually up to one-year post intervention.

#### **9.2 Procedures at each visit for both prospective-randomized studies**

At enrollment (Visit 1 / Day 1), patients will be randomized at ratio 1:1 into the investigational group (decolonization) and the control group (no decolonization). The study investigators will instruct the correct decolonization procedure. During the decolonization period, patients can also review the patient information leaflet of the set for details on the decolonization procedure. The questionnaire will be handed over to the decolonization patients.

The treatment period includes the following study visits:

- Visit 1 - Enrollment (Day 1)
- Visit 2 - End-of-Treatment (EOT) -Visit is the Day of Surgery or Day 1-2 after surgery
- Visit 3 - Test-of-Cure-Visit (TOC) (clinical surgical control) - Day 42 (+/- 14 days)
- Follow-up (eventually by phone call) for implant-related surgery after 1 year (+/- 2 months).

During the study visits, we assess the history, wounds, adverse events, and the functional status. We examine the patients according to the orthopedic standard, and add supplementary laboratory exams and radiology, only if clinically indicated.

##### **9.2.1 Enrolment (Visit 1)**

Information collected during routine pre-surgical consultation and during orthopaedic surgery is not study specific. This data will be used as general demographic information and medical history within the study in case of an orthopaedic infection and study participation.

If a patient appears to be eligible the following study-related procedures are performed:

1. Patient information and obtaining written informed consent.
2. Assign a study identification number.
3. Record/complete medical history and demographics.
4. Review inclusion/exclusion criteria.
5. Randomize the patient and handing out of the decolonization set.

##### **9.2.2 Visit 2 (End-of-Treatment)**

1. Record any concomitant medications as well as any additional interventions required
2. Adaptation of (empirical) antibiotic therapy, if not done before.
3. Assess all adverse events of therapy.

##### **9.2.3 Visit 3 (Test-of-Cure)**

Every effort will be made to ensure that final efficacy assessments (i.e., primary outcome data) are available for all subjects. As all our study visits are part of the routine surgical and postsurgical assessments, we do not expect major drop-out rates; or drop out in very exceptional situations (e.g. transfer to another service because of stroke, non-infectious postsurgical fatalities, etc.) Outpatients should return to the clinic (assessments can be performed in the hospital for inpatients), where the following assessments will be performed:

1. Assess anamnestically all past adverse events of surgery, the hospitalization and decolonization
2. Record clinical and microbiological infection and its treatment (if any)

#### 9.2.4 Follow-up visit at approximately 1 year (for implant-related orthopaedic surgery)

3. Anamnestic assessment of all past adverse events of surgery, the hospitalization and decolonization

Record of clinical and microbiological infection and its treatment (if any).

#### 9.2.5 Early Termination of Study Patients

Patients who withdraw consent or who, in the opinion of the investigator, are no longer able or eligible to participate in the study (including patients who require antibiotic therapy beyond EOT) will be early terminated. Where possible, such patients will complete an early-termination visit to undergo all assessments applicable to the corresponding (or next) scheduled study visit.

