The duration of pre-surgical decolonization is planned to be five days. However, when this pre-surgical time period is too short, the decolonization may also start at least 3 days before surgery and be continued up to 2 days post-surgery. During the post-surgery application, the patient will be washed with water and octenisan® by their treating nurses. The patient will also return the empty/used set and answer to a short questionnaire during their hospital stay. The study team will recuperate the questionnaire during hospitalization. We renounce on routine microbiological assessments of skin colonization, but the hospital's infection control can demand it for other reasons regarding infection control. Hence, skin colonization data will only be available for some selected patients that are screened for body carriage of antibiotic-resistant pathogens, according to the infection control recommendations in Switzerland.

There will be a Monitoring at study start, the interim analysis and at the end.

The primary study outcomes are unplanned revision surgery for SSI and wound problems at 42 days for all surgeries; or 1 year in case of an implant-related surgery. Secondary objectives are other unplanned revision surgeries for non-SSI reasons, all adverse events, as well as patient's subjective impression of the decolonization.

The treatment period includes the following daily study visits:

- Visit 1 - Enrollment (Day 1)
- End-of-Treatment (EOT) -Visit is the Day of Surgery or Day 1-2 after surgery
- Test-of-Cure-Visit (TOC) (clinical surgical control) - Day 42 (+/- 14 days)
- Further follow-up (eventually by phone call) for implant-related surgery - 1 year (+/- 2 months)

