### 2.7 Patient Information and Informed Consent

For the participation in the study, patients will be recruited/preselected by any of the investigators of the study. If patients match the inclusion criteria and do not meet any exclusion criterion, they will be informed by one of the study investigators, about the study, its nature, purpose, procedures involved, expected duration, participating investigators, potential risks and benefits and any potential discomfort the study could entail, during post-surgery visit when an orthopedic infection is diagnosed. Each participant will be informed that the participation in the study is completely voluntary and that he/she may withdraw from the study at any time and that withdrawal of consent will not affect his/her medical assistance and treatment in the future. No further screening requirements (other than the in- and exclusion criteria) exist.

All participants will be provided with a participant information sheet and informed consent form describing the study and entailing sufficient information for the participant to make an informed decision about their willingness to participate in the study. The patient information sheet and the consent form will be submitted to the CEC to be reviewed and approved. The information sheet provides the possibility to read through the study concept again and enables the patient to rethink the study participation without being pressured into deciding. If the participant decides to take part in the study, he/she will be asked to date and sign the informed consent form. The potential participant will be requested to read through the consent form and the information sheet carefully and to clarify any misunderstandings before signing. Once the patient dates and sign the informed consent form, one of the investigators will also date and sign the aforementioned document. The participant will be given a copy of the signed document. The original signed informed consent form will be retained as part of the study records.

The formal consent of a participant, using the approved consent form, must be obtained before the

participant is submitted to any study specific procedures.

The collection of the general consents for further use of health-related personal data and biological material is a standard at UKB. It is not study-specific.

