## 5. STUDY OUTCOMES

### Primary outcomes:

- Remission (and inversely superficial or deep-space SSI and revision surgeries for non-infected wound problems; composite primary outcome) at 6 weeks (and/or a 1 year for surgeries with implant)

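### Section 9.2.5 ends study participation for patients who need antibiotics after day 0-2, which contradicts the later outcome visits and risks outcome-dependent loss of primary-outcome data

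*Protocol*

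**What the plan says.** Section 9.2.5 lists who leaves the study early: those who withdraw consent, and those who in the investigator's opinion are "no longer able or eligible to participate in the study (including patients who require antibiotic therapy beyond EOT) will be early terminated". It adds: "Where possible, such patients will complete an early-termination visit to undergo all assessments applicable to the corresponding (or next) scheduled study visit".

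Section 9.2 fixes the reference point: "Visit 2 - End-of-Treatment (EOT) -Visit is the Day of Surgery or Day 1-2 after surgery". Visit 3 follows at day 42 (+/- 14 days), and implant patients have a further contact at 1 year (+/- 2 months).

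The primary outcome in section 5 is remission, or inversely "superficial or deep-space SSI and revision surgeries for non-infected wound problems; composite primary outcome", read at 6 weeks and/or 1 year. Sections 9.2.3 and 9.2.4 require the later visits to record any clinical and microbiological infection and how it was treated.

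On the analysis sets, 11.3.2 defines ITT as everyone randomized. The per-protocol (PP) set is completers without significant deviation, plus those counted as treatment failures. Section 11.4 says that missing outcome data make the patient a drop-out, and that major deviations count as drop-outs and leave both ITT and PP.

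Section 11.3.2 also contains a separate sentence: "Any analysis involving microbiological assessments will exclude patients without an assigned baseline pathogen".

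**The concern.** The event that triggers termination is linked to the outcome being measured. Patients on antibiotics at surgery, or operated on through infected skin, are excluded at entry (7.1). Antibiotics needed after EOT will therefore often be for a suspected or proven wound infection, although the protocol gives no data on how often. Ending participation at that point means that follow-up stops for reasons related to the outcome, before the 6-week or 1-year reading.

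Two harms follow. If the outcome is then missing, 11.4 makes the patient a drop-out. If the patient is instead kept in the Cox model of 11.3 and censored at termination, the censoring is not independent of the event risk. Either way the comparison can lose events, and can lose them unequally, in a trial where few events are expected.

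**Working it through.** **1. The provisions side by side**

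| Provision | Effect on a patient given antibiotics on, say, day 10 for a suspected SSI |
|---|---|
| 9.2.5 | Early-terminated; one visit if feasible |
| 9.2.3, 9.2.4 | Should be seen at day 42 and, with an implant, at 1 year, with infection and its treatment recorded |
| 9.2.3 | Primary outcome sought for all; drop-out expected only in exceptional situations |
| 8.4, 9.1.4 | Surveillance advised; adverse events, examination, laboratory values and vital signs recorded, usually for up to one year under clinical control; the primary outcome is not named |
| 11.3.2 | In ITT as randomized; in PP if a treatment failure, a term the protocol does not define |
| 11.4 | Drop-out if the outcome is missing; out of ITT and PP if classed as a major deviation |

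The first two rows cannot both be followed. The last two leave it open whether the patient is analysed.

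**2. The plan's own sample size**

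Inputs: 10% against 5% (11.1, 11.2), 80% power (11.2), two-sided 0.05 (11.3), 1:1 allocation (6.2.1).

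n = [1.960·√(2·0.075·0.925) + 0.842·√(0.10·0.90 + 0.05·0.95)]² / 0.05² = 434.4 per arm.

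With continuity correction: (434.4/4)·[1 + √(1 + 4/(434.4·0.05))]² = 473.6, so 474. This matches 11.2, which then rounds up to 500 per arm.

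**3. Expected events**

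500·0.10 = 50 and 500·0.05 = 25, together 75.

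**4. Power if a share f of events is lost in both arms**

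The protocol does not give f, so every value above zero is an assumption. Power = Φ[(d − 1.960·SE₀)/SE₁], where d is the difference in observed rates, SE₀ = √(p̄(1−p̄)(1/n₀+1/n₁)) and SE₁ = √(p₀(1−p₀)/n₀ + p₁(1−p₁)/n₁), without continuity correction.

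With no loss: (0.05 − 1.960·0.01666)/0.01658 = 1.046, so power is 85%.

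A lost event can be treated in two ways: the patient stays in the denominator as event-free, or leaves both numerator and denominator.

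| f | Events | Rates, kept as event-free | Power | Rates, excluded | Power |
|---|---|---|---|---|---|
| 0 | 50 / 25 | 10.0% / 5.0% | 85% | 10.0% / 5.0% | 85% |
| 10% | 45 / 22.5 | 9.0% / 4.5% | 81% | 45/495 = 9.1% / 22.5/497.5 = 4.5% | 82% |
| 20% | 40 / 20 | 8.0% / 4.0% | 76% | 40/490 = 8.2% / 20/495 = 4.0% | 77% |
| 50% | 25 / 12.5 | 5.0% / 2.5% | 55% | 25/475 = 5.3% / 12.5/487.5 = 2.6% | 58% |

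**5. Unequal loss, as an illustration**

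If 20% of control events and 10% of decolonization events were lost, 40 and 22.5 would remain. Kept as event-free: 8.0% against 4.5%, power 63%, and the risk ratio moves from 0.50 to 0.045/0.080 = 0.56. Excluded: 40/490 = 8.2% against 22.5/497.5 = 4.5%, power 65%, ratio 0.55. The opposite imbalance would exaggerate the effect. The documents do not say which is likelier.

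**6. The baseline-pathogen sentence**

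Participants are not operated on through infected skin or under antibiotics (7.1), and the Synopsis (Study Conduct) states: "We renounce on routine microbiological assessments of skin colonization". Almost no one could have an assigned baseline pathogen, so read literally the sentence empties any microbiological analysis, whether or not patients had an event. The primary outcome is judged clinically, by visual wound assessment with the treating physician deciding doubtful cases (9.1), and is not reached by this rule.

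**The case against.** The best defence is that the protocol never says terminated patients leave the primary analysis. ITT is all randomized, PP retains treatment failures, an early-termination visit is planned, 9.1.4 continues recording for up to about a year, 8.4 tells withdrawn participants to continue surveillance, and 9.2.3 promises every effort to obtain the primary outcome. Under section 5 an SSI is itself an event, so one recorded at or before termination already counts and a later revision adds nothing. Revisions for non-infected wound problems need not involve antibiotics at all. Section 11.4 states removal from ITT explicitly only for major deviations; that missing-outcome patients are also removed is a reasonable inference, not stated text.

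Most of this stands, and it limits the claim. A reader might infer that the rules remove the patients in whom the primary outcome occurs, or that later revisions are never counted. The documents do not support either reading. Nor do they support reading the baseline-pathogen sentence as a bias in the primary analysis, since it covers only microbiological analyses.

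The safeguards still do not close the gap. The early-termination visit is a single visit, held only if feasible, and cannot capture an implant revision months later. Section 9.1.4 does not name the primary outcome. Section 3.2.1 requires bacteria in at least two intraoperative samples for an orthopedic infection, so a patient treated on suspicion and terminated before any re-operation may not meet it. The Synopsis (Study Conduct) words the primary outcome as revision surgery; on that wording an SSI under antibiotics is not yet an event at termination.

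**Conclusion.** The contradiction between 9.2.5 and 9.2.3-9.2.4 is certain: it is current text and turns a usual consequence of SSI into a ground for ending participation. With 11.4 it permits informative loss of primary-outcome data. That loss is a risk the text creates, not a result it prescribes.

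The size is uncertain. With about 75 expected events, power falls from 85% to 76-77% if 20% of events are lost in both arms and to 55-58% if 50% are lost. These shares are assumptions, and the ranges reflect whether lost patients stay in the denominator. A reader might infer that the effect must be biased towards zero; that requires greater loss among controls, on which the documents give no data.

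The baseline-pathogen sentence is a secondary defect: unworkable, but without effect on the primary outcome. The text reads as if taken from an infection-treatment trial, but that is an inference and the finding does not depend on it.

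**What to change.** Reconcile 9.2.5 with 9.2.3, 9.2.4, 11.3.2 and 11.4:

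- In 9.2.5, remove antibiotic use after EOT as a ground for ending outcome follow-up. State that such patients complete the day-42 and, with an implant, the 1-year outcome assessments and stay in ITT. This concerns data collection only and says nothing about treatment.
- In 11.4, state that antibiotic treatment after surgery is not a reason for removal from ITT, and bring the paragraph into line with the definition of ITT as all randomized in 11.3.2.
- Secondary: delete the baseline-pathogen sentence in 11.3.2.

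The cost is a few sentences in an amendment, with ethics committee approval if judged substantial under 2.10. No visits are added, because 9.2.3 describes all study visits as part of routine care.

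Separately, and not part of this point, 2.7 places patient information "during post-surgery visit when an orthopedic infection is diagnosed", and 9.2.1 ties the use of baseline data to an infection. Both are clerical and should be aligned with the pre-surgical consultation in 7.2.
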